# ORASPORT study protocol: a prospective observational study on the impact of endurance physical activity on oral microbiology and immunology

**DOI:** 10.3389/froh.2025.1692359

**Published:** 2025-12-05

**Keywords:** oral health, oral microbiota, cytokines, endurance sports, protocol

## Abstract

**Clinical trial number:**

NCT05765422.


Oral health is closely associated with the composition and balance of the oral microbiota. This complex microbial ecosystem has emerged as a promising field of research, providing valuable insight into various health states (17). The oral cavity is a reservoir of a dense and diverse microbiota composed of thousands of bacterial, viral, and fungal species (18, 19). Under healthy conditions and with good oral hygiene, this microbial community maintains a stable composition that supports oral and systemic health. However, numerous factors that encompass oral hygiene practices, diet, psychological stress, systemic diseases, and smoking may disturb this fragile microbial balance. Similarly, to the gut microbiota dysbiosis, which has been associated with intestinal disorders (20, 21), autism (22), viral infections (23), and dietary changes (24, 25), alterations in the oral microbiome have been implicated in the onset of local conditions such as dental caries, candidosis, and periodontal diseases (26). Moreover, a growing body of evidence links oral dysbiosis to systemic diseases, including diabetes (27), Alzheimer's disease (28), Rheumatoid Arthritis (29, 30). In addition, the role of oral microbiota in carcinogenesis has gained attention, with studies highlighting its potential involvement in various cancers, including oral cancer (31, 32).

Previous studies have demonstrated that significant microbiological differences can be detected even with small sample sizes (33). Most investigates in this field involve approximately 20 participants, and the study conducted by Lamb et al. demonstrates statistically significant differences with as few as 10 participants per group (34). While the impact of physical exercise on the gut microbiota has been increasingly studied, its effects on the oral microbiota remain poorly understood (35). This study aims to explore the relationship between oral microbiota, immune profiles, and endurance training by examining immune markers and microbial signatures from oral samples. The primary objective of this cross-sectional study is to assess the oral microbiota and inflammatory status of healthy individuals engaged in varying levels of physical activity. Ultimately, this research seeks to identify specific microbiological and immunological signatures associated with both sedentary behavior and physical activity.

## Methods and analysis

2

### Outcomes

2.1

This cross-sectional study explores the relationship between oral microbiota composition, immune function, and physical activity levels in young, healthy individuals. The primary objective is to identify microbial and immunological oral signatures associated with varying levels of endurance activity. The microbial targets include a panel of commensal and pathogenic bacterial species, as well as human herpesviruses. By profiling the oral microbiota and salivary immune markers across a spectrum of physical activity, from sedentary to highly active individuals, we seek to identify potential microbial and immunological biomarkers associated with physical activity levels. All targeted microorganisms, cytokines, and recorded parameters are summarized in Table 1.

**Table 1 T1:** Study outcomes.

Principal study endpoints			
Commensal Bacteria	Pathogenic Bacteria	Human Herpes Viruses	Inflammatory Cytokines
*Streptococcus oralis*	*Porphyromonas gingivalis,*	HSV-1,	IFN-*γ*,
*Streptococcus gordonii*	*Streptococcus mutans,*	HSV-2,	IL-1β,
*Streptococcus salivarius,*	*Aggregatibacter*	EBV,	IL-2,
*Streptococcus sanguinis,*	*actinomycetemcomitans,*	CMV,	IL-4,
*Gemella haemolysans,*	*Corynebacterium matruchotii,*	VZV,	IL-6,
*Capnocytophaga gingivalis,*	*Fusobacterium nucleatum,*	HHV-6a,	IL-10,
*Micrococcus luteus,*	*Tannerella forsythia,*	HHV-6b,	IL-12p70,
*Rothia mucilaginosa,*	*Dialister pneumosintes,*	HHV-7,	IL-17A,
*Actinomyces naeslundii,*	*Filifactor alocis,*	HHV-8	TNF-α
*Granulicatella adiacens,*	*Treponema denticola,*		
*Veillonella parvula,*	*Prevotella intermedia,*		
*Eikenella corrodens,*	*Prevotella denticola,*		
*Actinomyces massiliensis*	*Prevotella melaninogenica,*		
	*Prevotella nigrescens,*		
	*Centipeda periodontii,*		
	*Campylobacter rectus,*		
	*Klebsiella pneumoniae,*		
	*Selenomonas sputigena,*		
	*Pseudomonas aeruginosa,*		
	*Haemophilus parainfluenzae,*		
	*Peptostreptococcus anaerobius,*		
	*Eubacterium nodatum,*		
	*Propionibacterium propionicum,*		
	*Parvimonas micra,*		
	*Megasphaera micronuciformis,*		
	*Porphyromonas endodontalis*		
Secondary study endpoints			
Caries	Gingival status	Tooth wear	Extra
• DMF index (WHO criteria)	• Loe and Silness Index (LSI)	• Absence	• Orthodontic retainer
• ICDAS system	• Plaque Index (PI)	• Presence	• MIH
	• Gingival recession (Miller)		• Fluorosis
			• Trauma
			• Tartar
Other study parameters			
• Socio-demographic factors			
• Salivary flow			
• Sport habits			
• Diet			
• General health status			
• Oral health status			
• Oral Health Impact Profile-14 (OHIP-14)			

The study's secondary objective is to assess and compare the dental health of participants across the different activity groups. Clinical oral health assessments will include the evaluation of dental caries, tooth wear, periodontal status, and other relevant clinical indicators. To reduce potential confounding biases, data will also be collected through structured questionnaires on diet, supplement use, general and oral quality of life (OHIP-14), socio-demographic characteristics, medication intake, lifestyle habits, healthcare (medical and dental), and oral hygiene practices.

### Study design and study population characteristics

2.2

ORASPORT is a single-center, cross-sectional, prospective pilot study. A total of 200 participants aged 18 to 30 years will be enrolled over a 30-month period.

Participants will be primarily recruited from the Sports and Dental Departments of Côte d'Azur University (France), as well as through local sports competitions. Additional recruitments will take place through researcher networks, university posters, and social media platforms. The inclusion criteria are: (i) age between 18 and 30 years old, (ii) male or female, and (iii) if practicing a physical activity, the primary sport must be an endurance activity (i.e., cycling or running).

Participants (*n* = 200) will be classified into three groups according to their physical activity levels: (i) Group 1 (*n* = 50): participants who do not meet the WHO recommendations, (ii) Group 2 (*n* = 100): participants who meet the WHO recommendations, defined as engaging in 150 to 300 min per week of moderate-intensity physical activity, or 75 to 150 min per week of vigorous-intensity physical activity, and (iii) Group 3 (*n* = 50): participants who exceeded the WHO recommendations. The larger size of Group 2 was chosen to account for the expected higher heterogeneity among participants meeting the WHO recommendations compared with those not meeting or exceeding them. The sex of the participants will be balanced as much as possible across the three groups during recruitment to account for potential differences in oral microbiota composition and immune profiles between men and women.

The sample size was not determined through a formal power calculation, as this is an exploratory pilot study designed to generate preliminary data and refine the methodology for a future large-scale investigation. Instead, the proposed sample size was estimated based on feasibility considerations. This number was deemed sufficient to capture variability within and between groups while remaining achievable within the study period. The results from this pilot study will inform the sample size calculation and group allocation strategy for subsequent confirmatory studies.

The non-inclusion criteria of the study are: (i) practicing more than 3 h of swimming per week, (ii) use of anti-inflammatory drugs within 48 h prior to participation, and (iii) use of antibiotics and/or probiotics within 3 weeks prior to participation. The 3-hour/week swimming threshold was chosen to minimize the potential confounding effect of chlorinated pool water exposure on the oral microbiota, as regular swimming activity has been reported to alter the oral microbial composition (36).

Participants may also be excluded if they withdraw their consent or oppose the use of their data or biological samples (i.e., withdrawal of non-opposition). All eligible participants will receive both verbal and written information about the study. Written informed consent will be obtained before enrollment.

Figure 1 provides an overview of the study design and procedures.

**Figure 1 F1:**
[figure not shown]
Schematic representation of the different stages of the ORASPORT pilot study. This figure outlines the complete recruitment process for participants in the ORASPORT study. Men and women aged 18 to 30 who express interest in participating will receive an information letter, a consent form, and a questionnaire to complete. The questionnaire includes items related to physical activity, diet, general health, and oral health. It is designed to collect essential baseline data and to classify individuals according to their physical activity level, based on World Health Organization (WHO) guidelines. All participants will undergo a standardized oral health assessment conducted by [name]. During this clinical examination, two types of saliva samples will be collected: an unstimulated whole saliva and a swab from the mandibular region between gingiva and tooth. Depending on the sample type, they will be stored at either −20 °C or −80 °C in the laboratory until analysis. Genomic DNA will be extracted from the samples using Qiagen kits (see Materials and Methods) for the subsequent identification of bacterial and viral content using the Biomark HD™ system (Standard Biotools). Cytokines analysis will be performed directly on whole saliva samples without prior DNA extraction. Finally, statistical analyses will be conducted to explore correlations between oral bacterial profiles, human herpesvirus presence, cytokine levels, and participant characteristics according to their physical activity levels.

### Visit procedure

2.3

Each participant will attend a single study visit that includes the completion of a personal questionnaire, a comprehensive oral health examination, and the collection of oral biological samples.

#### Personal questionnaire

2.3.1

Participants will complete a questionnaire designed to gather information across several domains linked to the study objectives. The questionnaire includes both validated tools and custom-designed sections and will be administered in paper format. It collects demographic data (age, sex, height, weight), medical and medication history, smoking status, and nutritional habits. In the nutritional habits section, the participants will be asked to report any specific dietary practices (e.g., vegetarian, vegan, gluten-free, lactose-free, flexitarian). To provide an overview of dietary behaviors, participants will be asked to self-identify the type(s) of diet they follow daily by selecting from a list of common dietary models (e.g., Mediterranean, Western, ketogenic, high-protein, high-carbohydrate, low-calorie). They will also be asked to estimate the relative frequency of adherence to each model, expressed as a percentage (totaling 100%). Additional items focus on sport-specific dietary habits, including the consumption of isotonic drinks (electrolyte-rich) drinks, energy drinks, energy gels, or energy bars. Participants will be asked to indicate the frequency, duration of use, and brand names where applicable.

Physical activity levels will be assessed using the International Physical Activity Questionnaire (IPAQ), which estimates overall activity in MET-minutes/week. Further details on sports-specific habits will also be recorded, including type, frequency, intensity, and duration of physical activities, as well as competition level and professional status. Participants will also report on their oral health status and behaviors, including the history of oral trauma, frequency of dental visits, and use of oral hygiene devices. Psychological and physiological stress levels will be assessed using Likert scales. Finally, the 14-item validated Oral Health Impact Profile (OHIP-14) will be employed to evaluate oral health-related quality of life.

#### Oral sampling

2.3.3

Saliva samples will be collected immediately following the oral health examination. Participants will be instructed to refrain from eating, drinking (including water), toothbrushing, or smoking for at least 30 min before sampling. An unstimulated whole saliva sample (2 mL) will be obtained via passive drooling (spit method) into sterile tubes. Additionally, a mucosal smear will be collected by swabbing the junction between the tooth and gingiva in the mandibular region using a sterile swab.

All biological samples will be transported to the MICORALIS Laboratory for processing and storage. Each saliva sample will be divided into two 1 mL aliquots. The first aliquots, intended for microbiological analysis, will be mixed with a virus-inactivating and nucleic acid-stabilizing buffer and stored at room temperature until DNA extraction. Extracted DNA will then be stored at −20 °C prior to high-throughput quantitative PCR analysis using the Biomark HD™ system. The second aliquot, intended for immunological analysis, will be treated with protease inhibitors (Pierce™ Protease Inhibitor Tablets, Thermo Scientific™) and immediately stored at −80 °C until cytokine quantification is performed using Meso Scale Discovery® (MSD) multiplex immunoassay technology. Gingival swabs will be stored at 4 °C for a maximum of 24 h or directly frozen at −20 °C to preserve DNA integrity and minimize nuclease activity or microbial overgrowth.

### Cytokines quantification

2.4

Cytokines levels will be measured using Meso Scale Discovery® MULTI-ARRAY® technology, an electrochemiluminescence-based patterned array system, offering high sensitivity, broad dynamic range, and multiplexing capability. The S-PLEX® kit was selected for its ability to simultaneously quantify 9 cytokines per sample with detection limits in the femtogram per milliliter (fg/mL) range. The procedure begins with washing the plate 3 times with 150 μL of PBS-T. Then, 50 μL of coating solution is dispensed into each well and incubated with shaking for one hour at room temperature. The plate is then washed, and 25 μL of blocking solution per well is added, followed by 25 μL of calibrator or sample. The plate is incubated at room temperature with shaking for 1.5 h. After this incubation, the plate is washed again, and 50 μL of TURBO-BOOSTTM antibody solution per well is added, followed by another 1 h incubation at room temperature with shaking. The second step, referred to as enhancement, involves adding 50 μL of enhancement solution to each well and incubating the plate at room temperature with shaking for 30 min. This is pursued by the addition of 50 μL of TURBO-TAGTM detection solution and a further 1-hour incubation at 27 °C with shaking. The final step, reading, consists of 3 additional washes with PBS-T and the addition of 150 μL of MSD GOLD Read Buffer to each well. The plate is then read immediately on an MSD instrument without further incubation.

### Microbiological analysis

2.5

DNA will be extracted from unstimulated saliva samples using the QIAamp DNA Blood Midi kit® (Qiagen, Cat. No.: 51185) and from swab samples using the QIAamp DNA Mini Kit® (Qiagen, Cat. No.: 51304), following the manufacturer's protocols. DNA quantification will be carried out using a microvolume spectrophotometer (Nanodrop Lite Plus™), and concentrations will be normalized to 10 ng/μL for saliva samples and to 1 ng/μL for swab samples.

Detection and quantification of the various oral microbiological species (see Table 1 for details) will be performed using the Biomark HD™ technology. This high-throughput technology allows the simultaneous detection of dozens of microbial targets across a large number of samples (41). All experiments performed with the Biomark HD™ system will be conducted using 96.96 IFC plates, following the manufacturer's instructions and reagent kits (Standard Biotools. No.: BMKM10-96.96-EG) supplied by Standard Biotools. We adhered to the protocol “Preamplification of cDNA for Gene Expression with Delta Gene assays”. Preamplification was performed under the following cycling conditions: 95 °C for 2 min, followed by 12 cycles of 95 °C for 15 s and 60 °C for 2 min. After Exonuclease I digestion, samples will be diluted 1:20 and processed following the protocol “Gene expression with the 96.96 IFC using Delta Gene assays on preamplified samples”, using the AX SsoFastTM EvaGreen® Supermix with low ROX (Bio-Rad, 172-5211). Quantitative amplification was conducted on the Biomark HD™ system using a microfluidic real-time PCR protocol optimized for microbial detection. The reaction workflow began with a UNG (Uracil-N-Glycosylase) treatment at 50 °C for 2 min to eliminate potential carryover contamination, followed by a hot start activation phase at 95 °C for 10 min. PCR amplification comprised 40 cycles of denaturation at 95 °C for 15 s and annealing/extension at 60 °C for 60 s, with fluorescence data acquisition at each annealing step.

Each sample will be analyzed in duplicate, including both primer and sample replicates, using 1.25 μL of template DNA, corresponding to 12.5 ng of DNA for saliva samples and 1.25 ng for swab samples. The data were analyzed with Real-Time PCR Analysis Software using automatically defined thresholds. Negative samples were defined as those with Cq values ≥ 35 for each species. Final results will be normalized using standard curves and expressed as copy numbers per microgram (µg) of DNA.

### Data visualization and analysis

2.6

The study will generate primarily quantitative data, including the abundance of each microorganism in saliva and mucosal samples, salivary inflammatory markers, oral health parameters (e.g., number of teeth, caries index, plaque index, gingival index, periodontal index), and variables derived from graded scoring system used to interpret data from health questionnaires. Data will be analyzed individually and compared across the three groups, classified according to their level of physical activity. The methodology is based on the development of an account matrix and the implementation of a relational database management system (RedCap™).

Descriptive statics will first summarize participant demographics and distributions. Univariate analysis will then be conducted using standard statistical tests appropriate for each variable (e.g., Student's t-test or Mann–Whitney *U*-test for continuous variables, ANOVA or Kruskal–Wallis for multiple-group comparisons, Chi-square tests for categorical variables, Pearson or Spearman correlation analysis).

To explore complex interactions between oral microbiota, immune markers, and clinical oral heath profiles, multivariate analysis such as principal component analysis (PCA) will be conducted. Subgroup comparisons based on qualitative criteria from self-reported questionnaires (e.g., dietary habits, smoking status) may also be considered. Potential confounding factors, including age, sex, smoking status, diet, and oral hygiene practices, will be accounted for using multivariate linear or logistic regression models, with covariates selected based on theoretical relevance and results from univariate analysis. This strategy ensures that observed associations reflect true relationships rather than confounded effects. Statistical significance will be set at *p* < 0.05.

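### The named parametric methods pool the variance, although the 50/100/50 split is justified by greater heterogeneity in Group 2; if that carries over to the outcomes, these tests are conservative and lose power

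*Protocol article*

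**What the plan says.** Section 2.2 (Study design and study population characteristics) fixes three groups: "Group 1 (*n* = 50): participants who do not meet the WHO recommendations", "Group 2 (*n* = 100): participants who meet the WHO recommendations" and "Group 3 (*n* = 50): participants who exceeded the WHO recommendations". It gives one reason for the unequal sizes: "The larger size of Group 2 was chosen to account for the expected higher heterogeneity among participants meeting the WHO recommendations". The comparison is with both other groups. No standard deviation, effect size or power figure is given, and the section says that no formal power calculation was made.

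Section 2.6 (Data visualization and analysis) calls for "standard statistical tests appropriate for each variable". Its examples are "Student's t-test or Mann–Whitney" (U-test) for continuous variables and "ANOVA or Kruskal–Wallis for multiple-group comparisons". Confounders are to be handled by linear or logistic regression, at a significance level of 0.05. No unequal-variance version of any test is named, and no variance criterion for choosing between tests is given.

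**The concern.** The two sections pull in different directions. Pooled-variance tests tolerate unequal spread fairly well when groups are the same size. At 50 v 100 they do not. The feature used to justify the unequal sizes is therefore the one that makes the named parametric tests misjudge their own noise.

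When the largest group is also the widest, it dominates the pooled variance. The standard error is then too large for comparisons of Group 2 with a smaller group, and for any Group 1 v 3 contrast taken from a model that pools all three groups. The tests reject too rarely. What is at stake is missed signals in a study meant to find candidate signatures and to inform the sample size of later studies. Part of the benefit of enlarging Group 2 is also given back at the analysis stage.

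**Working it through.** The article states no power or size figure, so there is none to reproduce; the sizes add up (50 + 100 + 50 = 200).

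**Inputs.** From section 2.2: n = 50/100/50, and Group 2 expected to be the more heterogeneous. From section 2.6: the tests and the 0.05 level (two-sided assumed). Assumed, because the article gives no values: normal outcomes, SDs 1/r/1 with r = 1.25, 1.5 or 2 and, for power, means −0.3/0/+0.3 in units of the Group 1 SD.

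**1. Student's t, Group 1 v 2, closed form.** True size = 2[1 − Φ(1.96 × SE_pooled/SE_true)]. At r = 1.5:
- pooled variance = (49 + 99 × 2.25)/148 = 1.836
- SE_pooled² = 1.836 × (1/50 + 1/100) = 0.0551
- SE_true² = 1/50 + 2.25/100 = 0.0425
- SE ratio = √(0.0551/0.0425) = 1.138, so the true size is 2.6%.

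For r = 1.25 and 2 the same formula gives 3.5% and 1.6%. Simulation with 100,000 replicates gives 3.6%, 2.6% and 1.6% for the three ratios. With the difference set for about 80% power, Student's t has 75%, 71% and 65%, against 79% for Welch's t each time.

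**2. Three-group test, simulated.** Results from separate simulation runs are shown as ranges where they differ.

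| r | ANOVA true size | ANOVA power | Welch's ANOVA power |
|---|---|---|---|
| 1 | 5.0% | 0.76 | 0.76 |
| 1.25 | 3.4–3.5% | 0.66 | 0.76 |
| 1.5 | 2.7–2.9% | 0.54–0.55 | 0.76 |
| 2 | 1.9–2.1% | 0.31 | 0.76 |

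The size of Welch's ANOVA stays at 5.0–5.1% for these ratios.

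**3. Group 1 v 3 contrast from a model pooling all three groups.** At r = 1.5 the pooled variance is (49 + 99 × 2.25 + 49)/197 = 1.63, although the variance in both groups compared is 1.0. The SE is inflated by √1.63 = 1.28. The true size is 2[1 − Φ(1.96 × 1.28)], about 1.2%. The true SE is √(2/50) = 0.2 and the difference 0.6, so power is Φ(0.6/0.2 − 1.96 × 1.276) = Φ(0.50) = 0.69, against about 0.85 with separate variances. At r = 2 the pooled variance is (49 + 99 × 4 + 49)/197 = 2.51; size is about 0.2% and power 0.46.

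**4. Stand-alone Group 1 v 3 t-test (50 v 50).** Size is 4.9–5.1% in every setting, and power equals that of Welch's t.

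**5. Rank tests.** With r = 1.5 and 2, Kruskal–Wallis has size 3.6% and 3.4%, and Mann–Whitney (Group 1 v 2) 3.7% and 3.3%. Kruskal–Wallis power in the step 2 setting is 0.65 and 0.56. They suffer less but are not immune.

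**6. Opposite direction.** With SDs 1.5/1/1.5 and 2/1/2, ANOVA size is 8.2% and 10.3%, and Student's t (Group 1 v 2) 8.4% and 11.0%. Welch versions stay at 5.0–5.1%.

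**The case against.** **The tests are only examples.** Section 2.6 asks for tests suited to each variable and pairs each parametric test with a rank alternative, and the article condenses a fuller protocol. This stands in part: the plan does not bind itself to pooled tests, and a variance rule may exist elsewhere. But the point is not a missing detail. Every option named for comparing continuous outcomes between groups is sensitive to unequal spread at these sizes, and the rank tests only soften the effect.

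**Heterogeneity among participants is not outcome variance.** Correct; the article does not say that any bacterium, virus or cytokine will vary more in Group 2. Yet enlarging a group for heterogeneity helps precision only if what is measured varies more there. The concern is therefore conditional on that reading, and its size rests on assumed SD ratios.

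**The power loss depends on the pattern of means.** This stands. The large ANOVA losses arise when Group 2 lies midway between the others. If only Group 2 is shifted, by the differences used for the t-test powers in step 1, ANOVA has 0.83, 0.80 and 0.75 against 0.84, 0.82 and 0.78 for Welch's ANOVA at r = 1.25, 1.5 and 2: a loss of at most about 3 points.

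**The calculations assume normal data.** Copy numbers with a Cq cut-off for negatives, and cytokine levels, will often need a transformation or a rank test. The figures are illustrations, not predictions for particular endpoints.

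**Two stronger readings are not supported.** A reader might infer that the plan inflates false positives to about twice 5%. That needs a smaller group to be the most variable, the reverse of section 2.2. It could happen for some of the many endpoints in Table 1, but it is not the plan's premise. A reader might also infer that every sedentary v highly active comparison is weakened. A separate two-sample t-test of Groups 1 and 3 does not use Group 2's variance, and logistic regression has no pooled residual variance. Only contrasts from a pooled three-group or adjusted linear model are affected.

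**Conclusion.** The concern holds in a limited form. If the heterogeneity expected in Group 2 extends to the outcomes, Student's t, ANOVA and ordinary linear regression are conservative for this design, and power is lost in three places: the three-group test, comparisons with Group 2, and Group 1 v 3 contrasts from a pooled model. Over the assumed SD ratios, Student's t for Group 1 v 2 loses about 4 to 14 points of power (79 − 75 and 79 − 65). For an ordered shift with Group 2 midway, ANOVA loses about 10 to 45 points (0.76 − 0.66 and 0.76 − 0.31). The upper ends require an SD ratio of 2, for which the article offers no evidence.

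The importance is minor to moderate. This is an exploratory pilot without a power claim, and section 2.6 leaves room to choose other tests. The change is still worth making, because Welch's ANOVA loses nothing material when the variances are equal.

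**What to change.** In section 2.6, name Welch's t-test and Welch's ANOVA as the parametric options in place of Student's t-test and ANOVA, applied on the log scale to copy numbers and cytokines where suitable. State that the adjusted linear models will use heteroscedasticity-consistent (HC3) standard errors, so that Group 1 v 3 contrasts from those models do not carry Group 2's variance. Keep Mann–Whitney and Kruskal–Wallis for variables with many non-detects. It would help if section 2.2 also said whether the heterogeneity expected in Group 2 refers to the measured outcomes.

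The cost is one sentence of analysis wording and a software option, with no new data or participants. The wording should be settled before the data are analysed; section 5.4 expects inclusion to end on April 15, 2026.

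### The primary objective is an activity-related signature, but no named analysis relates a joint marker profile to activity or measures how well a marker set discriminates

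*Protocol article*

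**What the plan says.** **Aim.** Section 2.1 (Outcomes) states: "The primary objective is to identify microbial and immunological oral signatures associated with varying levels of endurance activity". The Introduction words the primary objective more loosely, as to "assess the oral microbiota and inflammatory status of healthy individuals engaged in varying levels of physical activity", but closes by saying that the research looks for signatures of both sedentary behaviour and physical activity. Neither section defines a signature.

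**Analysis.** Section 2.6 (Data visualization and analysis) names three kinds of analysis:

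- Single-variable comparison by activity group: "Data will be analyzed individually and compared across the three groups, classified according to their level of physical activity". The tests offered include "ANOVA or Kruskal–Wallis for multiple-group comparisons", and "Statistical significance will be set at *p* < 0.05".
- A joint step, whose stated purpose is to look at how microbiota, immune markers and clinical findings interact: "multivariate analysis such as principal component analysis (PCA) will be conducted". Activity level does not appear in that sentence.
- Regression. Confounders such as age, sex, smoking, diet and oral hygiene "will be accounted for using multivariate linear or logistic regression models". The outcome and the exposure of these models are not stated.

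**Status.** Section 2.2 calls the study an exploratory pilot of 200 participants (50, 100 and 50 per group) without a formal power calculation. It says the results will inform later confirmatory studies.

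**The concern.** A signature, as distinct from a single biomarker, suggests a set of markers that together track activity level. PCA finds the directions of largest total variance without reference to activity group. In oral samples those directions may reflect hygiene, gingival status or smoking instead. The group comparisons do use activity, but take one variable at a time. The regressions are named for confounding.

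The article therefore leaves a gap between its aim and its named methods. The likely product is a PCA plot beside a list of markers with p below 0.05. Nothing in the plan would show whether that list distinguishes active from sedentary people beyond chance, yet section 2.2 and the Discussion pass the results on to later studies as planning data and candidate biomarkers.

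**Working it through.** The article gives no power, effect-size or discrimination figure, so there is nothing of its own to reproduce. The check has four steps.

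**1. Number of marker tests.** Table 1 lists 13 commensal bacteria, 25 pathogenic bacteria and 9 herpesviruses, so 13 + 25 + 9 = 47 organisms, plus 9 cytokines. (The Discussion gives the panel as 48; one more target changes nothing below.) Counting each organism once gives 47 + 9 = 56 markers. Counting saliva and swab separately gives 2 × 47 + 9 = 103.

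**2. What a nominal list contains when nothing is related to activity.** Expected false positives are m × 0.05. The chance of at least one, if the tests were independent, is 1 − 0.95^m.

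- m = 56: 56 × 0.05 = 2.8, and 1 − 0.95^56 = 0.94.
- m = 103: 103 × 0.05 = 5.15, and 1 − 0.95^103 = 0.995.

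**3. How discriminating such a list can look.** Null data were simulated with n = 50/100/50 and 400 datasets per structure, with markers either independent or sharing two assumed background factors. Markers significant at 0.05 were combined into a score for Group 3 against Group 1.

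- One run: at least one marker selected in 97 to 99% of datasets, mean apparent AUC 0.68 to 0.73, and 0.50 in fresh data.
- A second run, with 103 normal markers, Kruskal–Wallis selection and selected markers summed with the sign of their group difference: with independent markers, 99.5% of datasets, apparent AUC 0.71, fresh 0.50. With two background factors (loading SD 0.8), 92%, 0.64 and 0.51. Ten-fold cross-validation with the selection repeated inside each fold gave 0.50 in both cases.

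The apparent figure moves with the assumed structure. The fresh-data and cross-validated figures stay at about 0.50.

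**4. What PCA and the planned tests each detect when there is a signal.** Assumed: 56 markers, n = 50/100/50, 500 runs. Five independent markers shift with activity, and the other 51 are driven by two factors unrelated to activity.

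- Group 3 minus Group 1 of 0.5 SD: Kruskal–Wallis finds each true marker in 56% of runs. PC1 and PC2 differ by group in 5.8% and 6.4%.
- 0.8 SD: 94% per true marker, against 6.2% and 4.2%.
- No shift: 5.7% per marker, against 5.0% and 4.4%.

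Under this structure the leading components are blind to activity by construction. If activity were itself a dominant source of variation, PCA would show it. The planned single-marker tests do find the activity-related markers.

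**The case against.** **The plan does test markers against activity.** This stands. Section 2.6 compares variables across the three groups, Table 1 lists individual organisms and cytokines as principal endpoints, and section 2.1 also speaks of potential biomarkers. A reader might infer that nothing planned could find an activity-related marker, or that PCA is the only multivariate method named. The text supports neither: the group comparisons are there, and linear or logistic regression is also called multivariate.

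**PCA is given another job.** This also stands. Its stated purpose is to explore interactions among microbiota, immune markers and clinical profiles. The criticism is that no other named step does the joint work that the primary objective implies.

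**A reader might infer that the plan would miss real group differences that a global multivariate test would catch.** The calculations do not support this. With 8 markers shifted by 0.35 SD per group step and two strong background factors (200 datasets), the planned Kruskal–Wallis tests with Bonferroni correction detected a group difference in 97% of datasets, a PERMANOVA in 36%, and the first two components in 5%. With 12 markers shifted by 0.40 SD, the figures were 100%, 96% and 5%. In four further scenarios, the corrected planned tests and PERMANOVA gave 87% against 74%, 41% against 8%, 81% against 29%, and 100% for both. Low power is not the defect.

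**The article is condensed, and its wording makes PCA an example.** This has some force: a fuller protocol or analysis plan may name more. But the article does state its analyses, and their type does not match the stated primary objective.

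**It is an exploratory pilot, and candidate markers are to be validated later.** This limits the severity. It does not remove the need for an honest discrimination figure before candidates are carried forward.

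**Conclusion.** The point holds in a limited form. The article sets an activity-related signature as its primary objective, leaves signature undefined, and names no step that relates a joint marker profile to activity or estimates how well a marker set discriminates. The planned comparisons can produce a list of individual activity-associated markers, and for that purpose they work well.

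The size of the gap is the distance between how such a list can look and what it is worth. Under no effect, about 5 of 103 tests are expected to be positive, and the mean apparent AUC was 0.64 to 0.73 where the true value is 0.50. The expected count follows from the article's alpha and panel. The AUC range rests on assumed marker distributions and correlations and on one way of combining markers, so it is illustrative. Given the declared pilot status, this is an improvement worth making and does not invalidate the study.

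**What to change.** In section 2.6, keep the per-marker group comparisons, label PCA as descriptive, and add wording to this effect:

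*The signature is the set of markers retained by a penalised (for example elastic-net) regression of activity group on all microbial and cytokine markers. Marker selection and penalty tuning are carried out inside each fold of a repeated cross-validation. The selected markers and the cross-validated discrimination are reported, and both are exploratory.*

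A PERMANOVA for each compartment (saliva organisms, swab organisms, cytokines) may be added as an optional global summary. It should not be justified as more powerful than the planned tests.

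No new data, samples or visits are needed. Section 5.4 expects inclusion to finish on April 15, 2026, so the wording can be fixed before the full dataset is complete if it is added by then. The cost is some programming, and a cross-validated figure that will look less favourable than an in-sample one.
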